## Abstract

**Introduction:**

Progress in malaria control has stalled since 2015, highlighting the need for new control tools. The R21/Matrix-M (R21) malaria vaccine, a pre-erythrocytic vaccine recently approved by WHO for small children, may be one of these tools. This trial aims to assess whether seasonal mass vaccination with R21 reduces malaria transmission in The Gambia and Burkina Faso, two countries at the extreme of the transmission spectrum.

**Methods:**

This is a multi-centre open cluster-randomised controlled trial to assess the impact of mass vaccination with R21 on malaria transmission and morbidity. The trial will be implemented in eastern Gambia (low to moderate transmission) and Central Burkina Faso (intense transmission). Thirty medium-sized villages in The Gambia and 24 in Burkina Faso will be randomised (1:1) to either intervention or control arm. All eligible residents in intervention villages will receive R21 vaccinations in three-monthly rounds, from May to July 2024, prior to the malaria transmission season. A booster vaccine dose will be administered the following year, in June 2025. The primary outcome is malaria prevalence at peak transmission (November 2024). Secondary outcomes include safety and tolerability, incidence of clinical malaria, vaccination coverage and community acceptability, cost and cost-effectiveness of the intervention.

**Discussion:**

This is the first trial on seasonal mass vaccination aiming at reducing malaria transmission. Strengths of the study include its design as an adequately powered cluster-randomised trial and the inclusion of study sites with differing transmission intensity which will also provide safety and efficacy data for different age groups. Key challenges remain vaccine hesitancy and vaccination coverage. If successful, R21 seasonal mass vaccination will be an innovative intervention to accelerate malaria elimination efforts and reach the goal set in the Global Technical Strategy for malaria 2016–2030.

**Trial registration:**

Clinical trials.gov, NCT06578572. Registered on 27 March 2024.

## Background

Since 2000, the global burden of malaria has significantly reduced thanks to the large-scale implementation of control interventions. Between 2000 and 2023, an estimated 2.2 billion malaria cases and 12.7 million malaria deaths were averted worldwide, with 1.7 billion cases and 12 million deaths prevented in the World Health Organization (WHO) African Region alone [1]. During the same period, 26 countries successfully reported 3 consecutive years of zero indigenous malaria cases, and 18 of them were certified malaria-free by WHO [1]. Nevertheless, malaria remains a major public health problem, particularly in sub-Saharan Africa where progress has stalled since 2015 [2]. In 2023, there were an estimated 263 million malaria cases and 597,000 deaths, most of them in Africa [1].

Malaria affects disproportionately people experiencing disadvantage, poverty, and exclusion. It is both a consequence and a driver of poverty and inequality [3, 4]. A malaria-free world, besides preventing disease and deaths, would stimulate development and economic growth, improving the life of hundreds of millions of people. Nevertheless, achieving malaria elimination and possibly eradication would require new tools, innovative interventions and enhanced local capacities for the implementation of increasingly complex control measures. A vaccine against malaria could be one of these new tools.

Malaria vaccine development has so far targeted infants as malaria mortality is the highest in children under 5. However, mathematical models suggest that mass vaccination with a pre-erythrocytic vaccine (PEV) may substantially reduce population-level malaria transmission [5]. Two PEVs have been recently approved for use in small children by the WHO, namely RTS,S/AS01 (RTS,S) in October 2021 and R21/Matrix-M (R21) in October 2023 [6]. In Ghana, Malawi and Kenya, RTS,S, introduced by the national immunisation programmes in 2019 through large-scale pilot schemes, decreased hospital admissions for severe malaria by 32%, and all-cause mortality by 9% [7]. R21 is similar to RTS,S as it includes hepatitis B surface antigen (HBsAg) fused to the C-terminus and central repeats of the circumsporozoite protein (CSP), although it lacks the excess of HBsAg found in RTS,S. A double-blind, randomised, phase 3 trial across five sites in four African countries with differing malaria transmission intensities and seasonality reported in children aged 5–36 months a vaccine efficacy against multiple episodes of clinical malaria between 67 and 75% [8]. Both vaccines are safe and well tolerated [7–9].

Besides children < 5 years, older age groups are also at risk of malaria even though the risk of severe disease is lower than in younger age groups [10, 11]. In a context of decreasing but residual transmission, malaria can be an important cause of death among young adults [12]. Moreover, given R21 is a PEV, it protects against infection and may have a substantial effect on malaria transmission when administered to the whole population. We propose to carry out a cluster-randomised trial to determine the impact of seasonal R21 mass vaccination (all ages) on malaria transmission and morbidity. The trial will be implemented in 2 sites at the extreme of the transmission spectrum, i.e. in The Gambia where malaria transmission is moderate-to-low and in Burkina Faso where it is intense.

### Trial objectives

The primary objective of the trial is to compare in intervention and control clusters the prevalence (all age groups) of malaria at peak transmission after seasonal mass vaccination with R21 (3 monthly doses). Secondary objectives are to [1] assess the safety and tolerability of R21; [2] compare in intervention and control clusters the incidence of malaria infection and clinical malaria following the 3-monthly rounds of seasonal mass vaccination (primo-vaccination) and after one booster dose; [3] compare the malaria prevalence in both arms at the peak transmission after the 1-year booster dose; 4) determine the coverage of the intervention and the related socio-cultural factors; and [5] assess the community acceptability and cost-effectiveness of the intervention.

## Methods

This study protocol has been developed according to SPIRIT (Standard Protocol Items: Recommendations for Intervention Trials) guidelines [13].

### Study design and settings

This is a multi-centre open cluster-randomised controlled trial (ClinicalTrials.gov, NCT06578572) to assess the impact of mass vaccination with R21 on malaria transmission and morbidity. The trial follows a superiority framework, aiming to evaluate whether mass vaccination with the R21 malaria vaccine would result in a statistically significant reduction in malaria transmission and morbidity compared to no mass vaccination (control arm). The trial employs a parallel group design within a cluster-randomised framework, in which distinct clusters (e.g. villages) are randomly assigned to either the intervention arm (receiving mass vaccination) or the control arm (no vaccination). These groups are followed over time to assess differences in outcomes, allowing for a comparison of the vaccine’s effectiveness at the community level.

The study clusters are medium-sized villages with a population of 200–600 inhabitants. Study villages will be randomised in a 1:1 ratio to either the intervention or the control arm, and mass vaccination with R21 will be implemented in the intervention villages. All study villages, regardless of the study arm, will receive standard malaria control interventions as implemented by the National Programmes, and according to the National Strategic Plan for malaria control. These are Seasonal Malaria Chemoprevention (SMC), Intermittent Preventive Treatment during pregnancy (IPTp), Insecticide-Treated bed Nets (ITNs) and prompt diagnosis and treatment with an effective antimalarial drug.

The study will be implemented in Upper River Region (URR) in the eastern part of The Gambia and in Boussé District in the Central region of Burkina Faso. The URR is a region characterised by a long dry season from mid-October to mid-June, followed by a single short rainy season. Malaria transmission is moderate to low, and highly seasonal, with most malaria cases occurring during the rainy season and immediately afterwards, until December–January [14]. In November 2019, malaria prevalence by molecular methods was 12.8%, while the incidence rate of clinical malaria was 1.1/100 person-months [15]. In the Central region of Burkina Faso, malaria transmission is intense and seasonal. In 2020, a total of 103,314 cases of uncomplicated malaria and 2937 cases of severe malaria were reported. Most of them occurred over 5 months of the year, from July to November [16]. In both countries, malaria is predominantly due to *Plasmodium falciparum*, the main vector is *Anopheles gambiae* and the first-line treatment is artemether-lumefantrine.

### Village selection and Informed consent

The year preceding the implementation of mass vaccination, a baseline cross-sectional survey will be conducted in November, at the peak of malaria transmission, to identify villages with the required malaria prevalence. The survey will be implemented in 45 Gambian villages in the URR and 30 Burkinabe villages in Boussé District. In The Gambia, 30 villages (clusters) with a baseline *Plasmodium falciparum* prevalence by qPCR of at least 10% will be selected and included in the study; for Burkina Faso, 24 villages with a baseline malaria prevalence of at least 30% will be selected and included in the study. In each country, selected villages will be randomised to either intervention or control arm in a 1:1 ratio using a computer-generated algorithm (R version 4.2.2 and STATA version 16). Randomisation will be constrained such that the mean baseline prevalence in the intervention clusters is within ± 10% of the prevalence in the control clusters.

Following a thorough explanation of the study objectives and methods to the local authorities and the population of the study villages through sensitisation meetings, a census will be conducted to determine the size of the population, age structure and use of standard malaria control interventions. Afterwards, the study team, including field workers and nurses, will initiate individual consent procedures (before any study-related activity is implemented) to obtain written informed consent from all willing residents. Parents/guardians will provide written informed consent for their children, while adolescents 12–17 years old will be asked to provide an additional written assent. The consenting process will continue during the trial to include new residents and those missed at the time of the initial consenting process. Each resident will be assigned a unique census identification number.

### Study population and eligibility criteria

The target population for the R21 mass vaccination campaign are all eligible residents in the intervention villages. Residents in intervention villages will be enrolled for vaccination according to well-defined inclusion criteria as follows: [1] age ≥ 5 months, [2] willingness to comply with trial procedures, and [3] individual written informed consent. Exclusion criteria include the following: [1] pregnancy, [2] history of allergic disease or reactions likely to be exacerbated by any component of the vaccines, [3] any history of anaphylaxis in relation to vaccination, [4] known chronic illness, [5] any other significant disease, disorder or situation which, in the opinion of the investigator, may either put the participants at risk because of participation in the trial, or influence the result of the trial, or the participant’s ability to participate in the trial. To be vaccinated, all inclusion criteria and none of the exclusion criteria should be met. Prior to each vaccine dose, women of reproductive age (15 to 49 years old) will be systematically tested for pregnancy. Moreover, eligibility will be checked for all study participants during each vaccination round, and before the administration of the vaccine dose.

## Intervention

### Study vaccine: R21/Matrix-M

The R21 vaccine is made up of R21 and the adjuvant Matrix M. R21 is a recombinant protein vaccine that contains a component of the circumsporozoite protein (CSP) *of Plasmodium falciparum* fused to hepatitis B surface antigen in a form of non-infectious virus-like particle produced in yeast cell (Hansenula) [8]. R21 is manufactured by the Serum Institute of India (SIIPL). Matrix M, developed by Novavax, is a highly immunogenic saponin-based adjuvant that stimulates both humoral and cellular immune responses to vaccines.

Two vaccine doses will be available: a 5 µg of R21 adjuvanted with 50 µg of Matrix M (Recombinant, Adjuvanted) and a 10 µg of R21 mixed prior to administration with 50 µg of Matrix M (Recombinant). The 5 µg dose is formulated as a single vial of 1.24 ml, pre-packed for intramuscular injection for 2 eligible study participants aged < 15 years. The 10 µg dose is obtained by mixing prior to administration 2 vials of R21 (0.65 ml/vial) and 1 vial of Matrix M (0.5 ml). The mixing consists of withdrawing 0.5 ml from each vial of the R21 and adding them to the vial of 0.5 ml of Matrix M to obtain a mixture of 1.5 ml, which is gently mixed and then 0.75 ml (corresponding to a vaccine dose of 10 µg) is withdrawn and administered intramuscularly to eligible study participants aged ≥ 15 years.

### Mass vaccination

The study intervention*, *i.e., mass vaccination with R21, will be implemented over 2 years in 2024 and 2025, covering two malaria transmission seasons. Three monthly doses of R21 (primo-vaccination) will be administered to all eligible residents in intervention villages, starting from May 2024, with the aim of completing the vaccination schedule by July 2024, before the start of the malaria transmission season. A booster vaccine dose will be administered the following year, in June 2025, to all eligible individuals who received at least one vaccine dose the previous year. Residents who are eligible but not vaccinated in the previous year will be offered a complete vaccination schedule, i.e. 3 monthly doses, starting from April 2025 (Fig. 1).

**Fig. 1 Fig1:**
[figure not shown]
Trial timelines (SPIRIT figure). “*X*” indicates when the activity occurs

### Post-vaccination activities

In each village, during each series of vaccination, the first 100 vaccinated individuals will be actively visited at home daily for 3 consecutive days, and then at day 7 after the vaccination to collect local and systemic adverse events (AEs). All vaccinated individuals (or their parents for those < 18 years) will be requested to report to the study nurse stationed in their study village in case of any complaints or symptoms occurring within 28 days post-vaccination.

In each intervention village, 10 randomly selected individuals (≥ 3 years old) will have 1.5 ml of venous blood collected at 4 time points, i.e. prior to each monthly dose and 1 month after the third vaccine dose, for safety laboratory (haematology and biochemistry) tests.

Following primo-vaccination, a system of passive case detection will be established at local health facilities and within each study village where a study staff (nurse or fieldworker) will be stationed permanently throughout the study duration to record clinical malaria cases. All suspected malaria cases (patients with fever and/or history of fever without any other obvious illness) will be investigated with a malaria Rapid Diagnostic Test (RDT) and treated following the national guidelines. Axillary body temperature, a thick blood film for microscopy, and dried blood spots (DBS) on filter paper for later molecular analysis will be collected.

To estimate the incidence of malaria infection, 20 individuals per village in Burkina Faso and 30 individuals per village in The Gambia aged at least 6 months will be randomly selected and visited monthly at home after the completion of the primo-vaccination schedule. Before starting the monthly follow-up, they will be treated with a full dose of artemether-lumefantrine to clear any parasitaemia. During the home visits, the axillary body temperature will be measured and a finger prick blood sample for a thick blood film for later microscopy and DBS for later molecular analysis will be systematically collected until the end of the transmission season (December 2024). Similarly, during the dry season, three additional home visits will be conducted every 8 weeks ± 2 weeks between January and May 2025 and during the same period in 2026.

In all study villages, a cross-sectional survey to estimate the prevalence of malaria infection (all ages) will be carried out at peak transmission season (November) both after the primo-vaccination (Nov. 2024) and after the booster dose (Nov. 2025). One hundred individuals per village aged at least 6 months will be randomly selected, regardless of their vaccination status. All surveyed participants will be clinically examined, including measurement of the axillary temperature, and a finger prick blood sample will be collected for a thick blood film for later microscopy and DBS for later molecular analysis. Individuals with symptoms suggestive of clinical malaria will have a standard RDT performed on them. If positive, they will be treated with artemether-lumefantrine. A short questionnaire will be administered to collect information on recent travel history, history of clinical malaria, and use of preventive measures against malaria.

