### Study outcomes

The primary endpoint is the prevalence of malaria infection measured by molecular methods (qPCR) in all age groups as determined by a cross-sectional survey at the peak of the first transmission season, i.e. in November 2024, following the primo-vaccination. Secondary endpoints are as follows: [1] occurrence of AEs; [2] incidence of malaria infection in all age groups during the transmission season following primo-vaccination; [3] incidence of clinical malaria in all age groups following primo-vaccination; [4] prevalence of malaria infection by molecular methods in all age groups at peak transmission following the booster dose; [5] incidence of malaria infection in all age groups during the transmission season following the booster dose; [6] incidence of clinical malaria in all age groups following the booster dose; [7] coverage of the intervention and community acceptability; [8] cost of vaccine administration, both for the primo-vaccination and the booster dose; [9] incremental cost-effectiveness. Exploratory outcomes are prevalence of serological markers (AMA-1, MSP-1, GLURP, GexP, RH2030 and Etramp5.Ag1) at peak transmission after the mass vaccination campaign with 3 monthly doses and the booster dose.

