## Discussion

The SERVAL trial aims to determine the impact of seasonal mass vaccination with R21 on malaria burden, i.e. prevalence of infection, incidence of clinical malaria and malaria infections. This is the first time the potential effect of vaccinating the entire population with a vaccine developed for children under 5 years of age is being investigated. While the R21 vaccine was first tested in adults before progressing to phase II and III trials in children [22], there remains limited data on its efficacy in protecting older children and adults from infection. The administration of R21 vaccines to healthy volunteers both in the United Kingdom (UK) and Burkina Faso was safe and elicited similar IgG immune responses against the conserved central NANP repeat region of the pre-erythrocytic CSP [23]. Furthermore, in adult volunteers who received the standard regimen of three doses of R21 at four-week intervals and were then experimentally infected with malaria, the vaccine demonstrated an efficacy of 80% [22]. Mathematical models suggest that mass vaccination with a pre-erythrocytic vaccine may substantially reduce population-level malaria transmission [5]. Mass vaccination before the transmission season at a coverage between 60 and 80% may reduce malaria prevalence by 70–80%, while combining it with mass drug administration would almost interrupt transmission [24]. It is important to confirm or refute such predictions through large-scale trials especially given that some goals outlined in the WHO Global Technical Strategy 2016–2030 are lagging by over 60% [25]. Urgent new control tools and strategies are needed to regain progress towards malaria elimination and eventual eradication. The mass vaccination of the entire population with R21 could be one such approach.

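### As written, the November 2024 primary survey can include incidence-cohort members whom the study treated with an antimalarial in both arms, which could slightly inflate the relative reduction (minor)

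*Protocol article*

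**What the plan says.** The primary endpoint is qPCR prevalence, measured in "a cross-sectional survey at the peak of the first transmission season, i.e. in November 2024, following the primo-vaccination" (Study outcomes). The sampling rule is in Post-vaccination activities: "One hundred individuals per village aged at least 6 months will be randomly selected, regardless of their vaccination status".

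The same section sets up a second random sample for the incidence of infection: "20 individuals per village in Burkina Faso and 30 individuals per village in The Gambia aged at least 6 months will be randomly selected", to be "visited monthly at home after the completion of the primo-vaccination schedule". On treatment of this cohort it says: "Before starting the monthly follow-up, they will be treated with a full dose of artemether-lumefantrine to clear any parasitaemia".

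The cohort is defined per village, and Trial objectives compares infection incidence between intervention and control clusters, so the course is given in both arms. Mass vaccination sets the timing, "with the aim of completing the vaccination schedule by July 2024, before the start of the malaria transmission season", and gives no calendar date for the clearance course.

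In Sample size and statistical analysis, the primary comparison is a Welch t-test on cluster prevalences. The same section also describes a random-effects logistic regression adjusted for study month, age group, ITN use and baseline village prevalence. Neither has a term for study-given treatment.

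**The concern.** Both samples come from the same villages and the same age range, and nothing keeps them apart. Some people in the primary survey will therefore have had their infections cleared by the trial itself.

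The article describes R21 as a pre-erythrocytic vaccine. If it prevents new infections but does not remove those already in the blood, infections carried over from before vaccination dilute its relative effect on November prevalence. Among cohort members that dilution has been removed. The surveyed prevalence is then a mixture of untreated residents, for whom the question is asked, and a small drug-cleared group whose share depends on village size. The result at stake is a small shift, in the vaccine's favour, in the prevalence ratio or odds ratio of the primary endpoint.

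**Working it through.** The article gives no figure for this overlap, so there is none to reproduce. The 80% power statement is a separate matter and is not used here.

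**Inputs from the article.** Village size N = 200–600 (Study design and settings). Cohort size n = 20 (Burkina Faso) or 30 (The Gambia). Survey of 100 per village. Control prevalence p = 40% or 13.5%, and reduction of about 45%, so intervention prevalence 0.55p = 22% or 7.4%. ICC 0.17 or 0.10. Infection incidence 2.8 or 1.42 per person-year.

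**Assumptions.** A share s = 20–40% of November infections in untreated controls is carried over from before vaccination. The vaccine does not clear these. The drug clears all of them, and no cleared person is reinfected.

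**Step 1, overlap.** Cohort share w = n/N; expected number among the 100 surveyed = 100w.
- Burkina Faso: 20/600 = 3.3% to 20/200 = 10%, so 3.3 to 10 people.
- The Gambia: 30/600 = 5% to 30/200 = 15%, so 5 to 15 people.
- The hypergeometric chance of no overlap is largest at N = 600: 2.4% and 0.4%.

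**Step 2, timing.** If the course is given between late July and August, the interval to the November survey is about 3–4 months.

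**Step 3, effect on the contrast.** Cohort members lack the carried-over part s·p, so in the whole sample:
- control = p(1 − ws)
- intervention = p(0.55 − ws)
- difference = 0.45p for every w and s, i.e. 18.0 points in Burkina Faso and 6.1 in The Gambia, unchanged
- relative reduction = 0.45/(1 − ws)

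| Village size | Burkina Faso, s = 0.2 / 0.4 | The Gambia, s = 0.2 / 0.4 |
|---|---|---|
| 200 | 0.45/0.98 = 45.9% / 0.45/0.96 = 46.9% | 0.45/0.97 = 46.4% / 0.45/0.94 = 47.9% |
| 400 | 45.5% / 45.9% | 45.7% / 46.4% |
| 600 | 45.3% / 45.6% | 45.5% / 45.9% |

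The largest case (The Gambia, N = 200, s = 0.4) has control prevalence 13.5 × 0.94 = 12.7% and intervention prevalence 13.5 × 0.49 = 6.6%. The crude odds ratio moves from (0.07425/0.92575)/(0.135/0.865) = 0.514 to (0.06615/0.93385)/(0.1269/0.8731) = 0.487.

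**Step 4, a different bound.** Suppose instead that every treated person were still negative in November. Both arms are then multiplied by (1 − w), and the ratio stays at 0.55. In villages of 200 the difference shrinks from 18.0 to 16.2 points (Burkina Faso) and from 6.1 to 5.2 (The Gambia). That is a loss of contrast, not a gain for the vaccine.

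**Step 5, reinfection.** At the article's annual-average incidence, 1 − exp(−rate × time) over 3–4 months gives 50–61% (Burkina Faso) and 30–38% (The Gambia) of cleared controls infected at least once. These exceed the assumed control prevalences, so the real effect of clearance is probably well below Steps 3 and 4.

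**Step 6, precision lost by excluding the cohort.** The cluster-mean variance is proportional to [1 + (m − 1)ICC]/m.
- The Gambia, m from 100 to 85: 10.9/100 = 0.1090 to 9.4/85 = 0.1106, up 1.5%.
- Burkina Faso, m from 100 to 90: 17.83/100 = 0.1783 to 16.13/90 = 0.1792, up 0.5%.

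**The case against.** The strongest reply is that the primary test is unharmed. The Welch test compares cluster prevalences, and in Step 3 that difference does not move. This stands; only the relative measures shift.

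The size also rests on an assumed carry-over share that the article does not supply. At s = 0.4, new infections would have to fall from 0.6p to 0.15p, a 75% reduction, to give 45% overall. Ignoring reinfection pushes the figures up further. This stands too, so the table shows upper values under its assumptions.

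The article condenses a full protocol that may already settle whether cohort members are eligible for the survey. That is fair. Still, the rule as printed admits them.

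Three stronger readings are tempting and are not supported:
- **That the trial tests vaccine plus drug against nothing.** The Discussion says of mass vaccination that "while combining it with mass drug administration would almost interrupt transmission", but this concerns drug treatment of a population. Here 3–15% of residents are treated, in both arms. Within the cohort the contrast is vaccine plus clearance against clearance alone. Clearance in the intervention arm only could take the ratio from 0.55 to 0.55 × 0.90 = 0.495 or 0.55 × 0.85 = 0.467, but no such design is described.
- **That treatment falls only weeks before the survey.** The planned dates imply about 3–4 months, much of it in the transmission season.
- **That the November 2025 survey is affected in the same way.** The article does not say whether a cohort is cleared again, or newly drawn, in 2025.

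**Conclusion.** The concern holds in a small form. As written, the primary survey can include cohort members, and some overlap is near certain in most villages. Because both arms receive the clearance course, the absolute difference is essentially unaffected. The relative reduction could be overstated: 45% would read as 46–48% in villages of 200, about 0.5–1.4 points higher at 400, and less than 1 point higher at 600. These figures assume 20–40% carry-over, a vaccine that leaves existing infections in place, complete clearance and no reinfection; with reinfection the shift would be smaller. It would not by itself overturn a clear result. Severity is minor; the case for acting is that the remedy is almost free.

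**What to change.** For any survey not yet drawn, remove incidence-cohort members from the census list before selecting the 100. Even a village of 200 leaves about 170 people in The Gambia and 180 in Burkina Faso. Remove everyone selected for the cohort, not only those who took the course; because selection was random, those who remain are still a random sample of the village.

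For a survey already done, flag cohort members through the census identification number. Before any arm-level result is seen, prespecify the primary comparison with and without them and state which is primary. The timing matters, because excluding people after data collection changes the endpoint.

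If the full protocol already excludes the cohort, one sentence saying so is enough.

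The cost is one filter on a list or one extra analysis. Exclusion at analysis loses up to about 15 of 100 observations in the smallest Gambian villages and 10 in Burkina Faso, which raises the cluster-mean variance by about 1.5% and 0.5%.
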